### **7.3.1 Primary analyses**

The primary analysis is a mixed effect model comparing the change from baseline of isotime IC after six weeks of treatment, with terms of sequence, treatment, period as fixed effects, baseline as a covariate, and subject within sequence as a random effect.

Adjusted mean values as well as treatment contrasts will be presented together with the 95% confidence intervals.

The primary analysis will be performed on the FAS.

A sensitivity analysis for the primary endpoint will be conducted for the PPS. This will only be done if the FAS and per-protocol set differ by more than 10% in size of the FAS population.

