### **7.2 NULL AND ALTERNATIVE HYPOTHESES**

The treatment difference with tiotropium to placebo will be tested for isotime IC change from baseline at the level of  $\alpha = 0.05$  (two-sided). The primary hypothesis can be written as follows:

H0: Mean change from baseline of isotime IC after six weeks of treatment with tiotropium = Mean change from baseline of isotime IC after six weeks of treatment with placebo

H1: Mean change from baseline of isotime IC after six weeks of treatment with tiotropium ≠ Mean change from baseline of isotime IC after six weeks of treatment with placebo

Different baseline values will be used for the two treatment periods of the cross-over study.

Visit 3 will be the baseline for the first period, while Visit 5 (after wash-out) will be the baseline for the second period.

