### **7.3.2 Secondary analyses**

The mixed effect model as described for the primary endpoint will be performed for all continuous secondary endpoints. The adjusted mean values as well as the treatment contrasts will be presented together with the 95% confidence intervals.

For constant work rate exercise duration, log transformation will be applied before taking the difference from baseline.

For evaluation of perception of improvement on the exercise test, analysis will be exploratory only and will be summarized descriptively.

For categorical endpoint (the locus of symptom limitation), frequency tables by visit as well as a shift table of baseline versus six weeks after treatment will be provided.

All other data, including baseline demographics, baseline disease data, concomitant medication use, will be summarised descriptively using appropriate methods.

All secondary analyses will be performed on the FAS.

The other endpoints comparing COPD patients with Age / Gender Matched Controls will be summarized descriptively, with 95% confidence interval for continuous variable. The first 100 randomized patients and the Age / Gender Matched Controls will be included in the analyses.

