### **7.6 DETERMINATION OF SAMPLE SIZE**

Based on the post-hoc analyses of the GOLD stage II patients in previous parallel Studies 205.131 and 205.223, and recent publication (4), it is deemed reasonable to assume that the effect between once-daily administration of tiotropium with placebo on IC will be 100 ml in GOLD stage I / II patients, and the standard deviation of change from baseline will be 340 ml. By assuming a correlation,  $r$  between the changes from baseline of the two treatment periods for the same patient, the variance of the within-patient difference can be calculated as:  $\text{var1} + \text{var2} - 2 * r * \sqrt{\text{var1} * \text{var2}} = (340\text{ml})^2 + (340\text{ml})^2 - 2 * r * (340\text{ ml} * 340\text{ ml})$ , where var1 and var2 are the variances of the change from baseline in

the first and second treatment periods, respectively. Various combinations of correlation and power are used to feed in nQueryAdvisors 6.01 MOT0-1 (one-sample t-test) with the following results:

Table 7.6: 1                      Calculated power and associated sample size (SD=340 ml, delta=100 ml)

| Correlation | SD of within-subject difference
between two periods | Effect size  | Power     | N          |
|-------------|--------------------------------------------------------|--------------|-----------|------------|
| 0.3         | 402                                                    | 0.249        | 90        | 172        |
| 0.4         | 372                                                    | 0.268        | 90        | 148        |
| 0.5         | 340                                                    | 0.294        | 80        | 93         |
| 0.5         | 340                                                    | 0.294        | 85        | 106        |
| 0.5         | 340                                                    | 0.294        | 90        | 124        |
| 0.6         | 304                                                    | 0.329        | 80        | 75         |
| 0.6         | 304                                                    | 0.329        | 85        | 85         |
| 0.6  | 304                                             | 0.329 | 90 | 100 |

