In a previous cross-over exercise Study 205.334, which comparing eight-weeks treatment with tiotropium plus salmeterol versus the fixed combination of fluticasone and salmeterol inpatients with COPD, only the first baseline value was collected. If the second baseline value is assumed to be the same as the first baseline, it showed a correlation of 0.5 between the two periods in terms of the change from baseline. However, this study had a relatively low correlation between the two post-dose IC values. Based on the information, it is deemed reasonable to assume a correlation of 0.6 between the changes from baseline of the two treatment periods.

Using a correlation of 0.6 and a type one error rate of 0.05 (two-sided), the sample size with 90% power to detect a 100 ml difference in IC change from baseline requires 100 patients in the analysis set. Assuming a drop-out rate of 20%, a total of 124 patients need to be randomized to ensure 100 completed, as well as to accommodate the block size of four in randomization.

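### The primary model gives the two period baselines one common slope beside a random patient effect; this is valid and meets the stated power, but gives up precision that separate slopes would recover at almost no cost.

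*Protocol*

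**What the plan says.** Section 7.3.1 states the primary model for change from baseline in isotime IC "with terms of sequence, treatment, period as fixed effects, baseline as a covariate, and subject within sequence as a random effect". Section 7.1 and the synopsis list the same terms. Baseline is not one value per patient. Section 7.2 states: "Visit 3 will be the baseline for the first period, while Visit 5 (after wash-out) will be the baseline for the second period".

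Section 7.3.2 extends the form: "The mixed effect model as described for the primary endpoint will be performed for all continuous secondary endpoints". Section 7.3 admits a patient to the full analysis set only if both week-6 values (Visits 4 and 6) are present. Section 7.4 fills a missing baseline with the patient's other baseline.

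For sample size, Section 7.6 assumes that "the standard deviation of change from baseline will be 340 ml" and that the two periods' changes correlate at 0.6. It uses a one-sample t-test on the within-patient difference, without a covariate, and concludes that "the sample size with 90% power to detect a 100 ml difference in IC change from baseline requires 100 patients in the analysis set".

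**The concern.** A baseline that varies within the patient carries two kinds of information. Between patients, someone with a high IC at baseline has a high IC after dosing, so change depends only weakly on baseline. Within a patient, two baselines ten weeks apart may differ mainly by visit-to-visit noise. A baseline that is high by chance is then followed by a smaller change, and the slope of change on baseline can approach -1.

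Because both post-dose values are required, the treatment effect is estimated from within-patient differences, and only the within-patient slope can remove baseline noise from it. A model with one slope estimates a weighted compromise, which the large spread of IC between patients pulls towards the weak relation. At stake are the width of the confidence interval and the power for the primary endpoint. The same applies in form, though no size was calculated, to the continuous secondary endpoints that use this model.

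**Working it through.** **Protocol inputs (Section 7.6).** Effect 100 ml, SD of change 340 ml, correlation of changes r = 0.6, two-sided 0.05, N = 100.

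**The plan's own figure.** SD of the within-patient difference = 340 × √(2 × (1 − 0.6)) = 304 ml. The exact one-sample t-test gives N = 100 with power 90.3%. All eight rows of Table 7.6:1 reproduce.

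**Assumptions, because the protocol gives no figure.**
- SD of baseline isotime IC: 400 to 700 ml.
- k, the within-patient correlation between a period's baseline and its post-dose value: 0 to 0.75.
- r arises from a patient-specific response shared by both periods. Visit noise then has variance e² = (1 − r) × 340² / 2.

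**Variance of the within-patient treatment difference.**
- Unadjusted change: 4e². At r = 0.6 this is 2 × 0.4 × 340² = 92,480, SD 304 ml, the planning value.
- Separate slopes: 2e²(1 + k). At r = 0.6 and k = 0, 0.25, 0.5 this gives SD 215, 240 and 263 ml.
- One common slope β on the post-dose scale (β = 1 + the slope for change): 2e²(1 + k) + (β − k)² × 2e² / (1 − k).

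The variance ratio, common to separate, is therefore 1 + (β − k)² / (1 − k²). It is 1 only if the common slope equals the within-patient slope k.

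**Simulation.** The stated model was fitted by REML to 3,000 trials per row, N = 100. SEs are empirical, in ml.

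| r | Baseline SD | k | Common slope (change) | SE common | SE separate | SE unadjusted | Variance ratio | Power common | Power separate |
|---|---|---|---|---|---|---|---|---|---|
| 0.6 | 400 | 0 | -0.40 | 24.9 | 21.4 | 30.0 | 1.36 | 98.0% | 99.6% |
| 0.6 | 700 | 0 | -0.13 | 28.9 | 21.8 | 30.8 | 1.77 | 92.5% | 99.3% |
| 0.6 | 600 | 0.25 | -0.17 | 28.4 | 24.3 | 30.7 | 1.36 | 93.9% | 98.2% |
| 0.6 | 600 | 0.5 | -0.15 | 28.2 | 26.5 | 30.1 | 1.13 | 93.1% | 95.7% |
| 0.6 | 600 | 0.75 | -0.12 | 29.6 | 29.0 | 31.0 | 1.04 | 92.1% | 92.5% |
| 0.5 | 600 | 0.25 | -0.17 | 31.7 | 26.9 | 34.3 | 1.39 | 87.7% | 95.3% |

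The formula agrees. In the second row β = 1 − 0.13 = 0.87, so the ratio is 1 + 0.87² = 1.76. In the fifth row β = 0.88, so it is 1 + 0.13² / 0.4375 = 1.04.

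In these runs the mean estimate under the common slope was 99 to 101 ml for a true 100 ml, and model SEs matched empirical ones.

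**Lower correlation of changes.** Assume an intraclass correlation of 0.8 and independent visit noise (k = 0), so the baseline SD is √(e² / 0.2).
- r = 0.3 (e² = 40,460, baseline SD 450 ml): SE 34.3 against 28.6 ml; power about 82% against 92%.
- r = 0 (e² = 57,800, baseline SD 538 ml): SE 42.8 against 34.1 ml; power about 63% against 84%.

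The unadjusted SE, 340 × √(2(1 − r)) / 10, is 40.2 ml at r = 0.3 and 48.1 ml at r = 0. The common slope still improves on it.

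**The case against.** The strongest reply is that nothing fails under the protocol's own assumptions. At r = 0.6 the stated model reaches about 92% to 98% power, above the 90% claimed. It was more precise than the unadjusted change score, on which N = 100 rests, in every scenario run. The estimate is unbiased and type I error was at or below 5%. All of this stands.

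A reader might infer that the model wastes much of the cross-over's advantage. The documents do not support that. A parallel design with SD 340 ml would need 2 × 243 = 486 patients against 100, and most of that saving remains. Nor does baseline noise pass almost undiminished into the contrast. A common slope of -0.19, typical of these settings, leaves (1 − 0.19)² = 66% of the baseline-noise variance when k = 0.

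A reader might also take 63% against 84% as the expected power. Those figures belong to r = 0, whereas the protocol plans on 0.6, reports 0.5 from an earlier study and tabulates nothing below 0.3. At r = 0 the unadjusted analysis has only 54% power, so most of the shortfall comes from the missing correlation. Lower values of r are still worth considering. The 0.5 in Section 7.6 came from subtracting the same baseline twice, and with independent visit noise that alone gives covariance s² over variance 2s², or 0.5. It is weak support for 0.6 with two separate baselines, but it does not show that r is 0.

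Finally, one could leave this to the statistical analysis plan. The protocol does defer details there, but it names every term of the primary model, and a plan that split the baseline would depart from that wording.

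**Conclusion.** The point holds as a free improvement, not as an error that threatens the trial. The model as written forces one slope on two relations and forgoes precision whenever they differ. At r = 0.6 the treatment variance is about 4% to 77% larger than with separate slopes, equivalent to analysing about 96 down to 57 of 100 patients. Where the true value lies depends on the SD of isotime IC and on the within-period correlation, neither of which the protocol gives. A strong within-period correlation makes the loss negligible. The consequence for power is small at the planned correlation and grows as the correlation falls. No scenario run showed the split to be less precise. For the secondary endpoints the argument applies in form only, since no SDs or correlations are given.

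**What to change.** In Section 7.3.1, with matching edits in Section 7.1 and the synopsis, replace the single baseline term by two covariates: the patient's mean of the Visit 3 and Visit 5 baselines, and the period baseline minus that mean. Keep sequence, period, treatment and the random patient effect.

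In Section 7.3.2, use the same form for continuous secondary endpoints that have a baseline at both Visit 3 and Visit 5, on the log scale for exercise duration. Exempt rescue medication use: Section 6.2.1 gives it only a run-in baseline, so its deviation would be zero for every patient and could not be estimated. Add a note to Section 7.4 that a baseline imputed from the other visit gives a deviation of exactly zero, so that such patients contribute nothing to the within-patient slope.

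The cost is one degree of freedom and a few sentences, settled before unblinding. No patients, visits or data are added.

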### **7.3.2 Secondary analyses**

The mixed effect model as described for the primary endpoint will be performed for all continuous secondary endpoints. The adjusted mean values as well as the treatment contrasts will be presented together with the 95% confidence intervals.

For constant work rate exercise duration, log transformation will be applied before taking the difference from baseline.

For evaluation of perception of improvement on the exercise test, analysis will be exploratory only and will be summarized descriptively.

For categorical endpoint (the locus of symptom limitation), frequency tables by visit as well as a shift table of baseline versus six weeks after treatment will be provided.

All other data, including baseline demographics, baseline disease data, concomitant medication use, will be summarised descriptively using appropriate methods.

All secondary analyses will be performed on the FAS.

The other endpoints comparing COPD patients with Age / Gender Matched Controls will be summarized descriptively, with 95% confidence interval for continuous variable. The first 100 randomized patients and the Age / Gender Matched Controls will be included in the analyses.

### **7.3.3 Safety analyses**

All treated patients will be included in the safety analysis. In general, safety analyses will be descriptive in nature and will be based on BI standards. No hypothesis testing is planned prospectively.

The number of patients with adverse events during the treatment periods will be summarized. An adverse event will be assigned to the treatment at onset. Any adverse events, which occur in Period 1 or wash-out, will be assigned to the treatment in Period 1. Any adverse events, which occur in Period 2 or within 30 days after the last study drug intake in Period 2, will be

assigned to the treatment in Period 2. AEs before Period 1 will be assigned to screening. AEs after 30 days from last study drug intake will be assigned to post-treatment.

Frequency, severity, and causal relationship of adverse events will be tabulated by system organ class and preferred term after coding to the current version of MedDRA.

Blood pressure and pulse rate will be presented for each treatment using descriptive statistics.

Physical examination findings (i.e., vital signs) determined at the end of the double-blind treatment period will be compared with those recorded at the beginning of the study.

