| Clinical phase:                                       |                                | IV                                                                                                                                                                                                                                                                                                                                                                                                                                                                                                                                                                                                                        |  |
| Objectives:                                           |                                | To determine the effects of tiotropium on lung dynamic hyperinflation due to airflow limitation as well as on symptom limited exercise compared to placebo in symptomatic patients with early stage COPD.

An additional objective is to characterize the mechanisms of exercise limitation and describe daily physical activity in patients with early stage COPD compared to Age / Gender Matched Controls.                                                                                                                                                                                                       |  |
| Methodology:                                          |                                | Randomized, double-blind, two-period cross-over trial: Two six-week treatment periods are separated by four-week wash-out.                                                                                                                                                                                                                                                                                                                                                                                                                                                                                                |  |

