## 4.2.2 Restrictions

Table 4.2.2: 1 Permitted medications and medication restrictions

| Drug Class                       | Sub-class                                                                          | Prior to study | Study Period    |                         |                  |
|----------------------------------|------------------------------------------------------------------------------------|----------------|-----------------|-------------------------|------------------|
|                                  |                                                                                    |                | Baseline Period | Treatment Period        | Follow up Period |
| Corticosteroids                  | Inhaled corticosteroids                                                | not permitted  | not permitted   | not permitted           | not permitted    |
|                                  | Oral corticosteroids                                                   | not permitted  | not permitted   | not permitted           | not permitted    |
| Beta-adrenergics / Beta blockers | Inhaled short-acting beta-adrenergics                                  | permitted      | rescue   | rescue           | permitted        |
|                                  | Inhaled long-acting beta-adrenergics                                   | permitted      | permitted       | permitted               | permitted        |
|                                  | Oral beta-adrenergics                                                              | not permitted  | not permitted   | not permitted           | not permitted    |
|                                  | Beta blockers                                                                      | not permitted  | not permitted   | not permitted           | not permitted    |
| Anticholinergics                 | Short-acting anticholinergics 
(inhalation aerosol and nasal spray) | permitted      | wash-out        | not permitted    | permitted        |
|                                  | Long-acting anticholinergics                                           | wash-out       | not permitted   | study medication | permitted        |

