| Miscellaneous                    | Other investigational drugs                                            | wash-out       | not permitted   | not permitted           | not permitted    |
|                                  | Cromolyn sodium / nedocromil sodium                                    | not permitted  | not permitted   | not permitted           | not permitted    |
|                                  | Antihistamines, antileukotrienes                                                   | permitted      | permitted       | permitted               | permitted        |
|                                  | Methylxanthines                                                                    | not permitted  | not permitted   | not permitted           | not permitted    |
|                                  | Mucolytics                                                                         | permitted      | permitted       | permitted               | permitted        |

1. Not allowed within 6 weeks prior to Visit 1
2. Must have at least an 8-hour washout prior to Visit 1 and all other visits during the protocol
3. Must have at least a 36-hour wash-out prior to Visit 1 and all other visits during the protocol
4. Must have at least a 36 hour wash-out prior to Visit 1 and all other Visits during the protocol
5. e.g. ipratropium bromide (Atrovent®): Must have at least an 8-hour washout prior to Visits 1 & 2 and must be discontinued at least 8 hours prior to Visits 3 and 5
6. e.g. tiotropium bromide (Spiriva®): at least a two week washout prior to Visit 1 and at least four week washout prior to Visit 3
7. washout of at least one month or six half lives (whichever is greater)
8. Intranasal allowed only if prescribed for conditions other than asthma

Patients using long-acting anticholinergics such as tiotropium may switch to a short-acting anticholinergic therapy such as ipratropium bromide (Atrovent®) as maintenance bronchodilator therapy during the baseline period; however, the patient must discontinue the

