long-acting anticholinergics at least two weeks prior to Visit 1 (Screening Visit) and at least four weeks ( $\pm 2$  days) prior to Visit 3 (Randomization Visit). The patient must discontinue ipratropium bromide at least 8 hours prior to Visit 3 (randomization visit). Patients who use ipratropium bromide during the baseline period prior to Visit 3 should resume use during the wash-out period between Visits 4 and 5 and then must discontinue ipratropium bromide again at least 8 hours prior to Visit 5.

Patients using fixed combination anticholinergic / short-acting beta adrenergic therapies such as Berodual®, Combivent® and Duovent® should be switched to the mono-product ipratropium bromide (e.g., Atrovent®) during the baseline period (without a change in the anticholinergic dose). The patient must discontinue ipratropium bromide at least eight hours prior to Visit 3 (Randomization Visit). Patients who use ipratropium bromide during the baseline period prior to Visit 3 should resume use during the wash-out period between Visits 4 and 5 and then must discontinue ipratropium bromide again at least 8 hours prior to Visit 5.

Refer to Section 5.1.2 for medication restrictions prior to PFTs.

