### 6.2.3 End of trial and follow-up (Visit 7)

Following the end of the 2 x six-week cross-over period, patients will be followed up for an additional 30 days. They will be phoned at the end of this period (Visit 7) and their smoking status, adverse events and concomitant therapies will be recorded.

The clinical monitor must be consulted on all persistently abnormal tests and SAEs until it is agreed that follow-up is no longer necessary.

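### Wash-out and 30-day follow-up adverse events are charged to the preceding study treatment although non-study anticholinergics may be taken then, so some class events can be tabulated under placebo

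*Protocol*

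**What the plan says.** Protocol Section 7.3.3 opens with a general principle: "An adverse event will be assigned to the treatment at onset". It then fixes two windows. For the first: "Any adverse events, which occur in Period 1 or wash-out, will be assigned to the treatment in Period 1". The second goes to the Period 2 treatment, in a sentence that begins: "Any adverse events, which occur in Period 2 or within 30 days after the last study drug intake in Period 2, will be". No exception or flag is given for events that start while the patient takes another anticholinergic.

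The synopsis gives the schedule: "Two six-week treatment periods are separated by four-week wash-out". After the second period, Section 6.2.3 says "patients will be followed up for an additional 30 days".

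Section 4.2.2 governs other medication in these windows. Patients who used ipratropium in the baseline period "should resume use during the wash-out period between Visits 4 and 5", and stop again at least 8 hours before Visit 5. In Table 4.2.2: 1 the long-acting anticholinergic row ends, for the treatment and follow-up columns, with "study medication | permitted". Short-acting anticholinergics are also permitted in follow-up. Footnote 6 shows which drug the long-acting row has in mind: "e.g. tiotropium bromide (Spiriva®): at least a two week washout prior to Visit 1".

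**The concern.** The two attribution windows run well past the last dose, into time when no study treatment is being given and when a drug of the test product's own class, or the test product itself as marketed, may be in use. A placebo-first patient who resumes ipratropium in the wash-out and reports dry mouth is counted under placebo. So is a placebo-second patient who starts marketed tiotropium after Visit 6 and has trouble passing urine. The patient leaflet in Appendix 10.1 lists both of these as common effects of tiotropium and counts ipratropium among the anticholinergics.

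Section 2.5 lists only adverse events and withdrawals due to them as safety endpoints, although the synopsis adds vital signs. The event tables therefore carry most of the safety result. At stake is how clearly they show class effects against placebo.

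**Working it through.** The plan states no figure for this point, so there is nothing to reproduce. The check has two parts: the length of the windows, and an illustration of what they could do.

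**1. Off-drug share of each window** (synopsis, Flow Chart, Section 6.2.3)

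Share = off-drug days / (on-drug days + off-drug days)

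- Period 1: 28 / (42 + 28) = 28/70 = 40.0%
- Period 2: 30 / (42 + 30) = 30/72 = 41.7%
- Both: 58/142 = 40.8%

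The Flow Chart allows 3 days either way at Visits 4 and 5. With Visit 4 on day 45 and Visit 5 on day 67, the Period 1 share is 22/67 = 33%. With days 39 and 73, it is 34/73 = 47%.

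**2. Illustration A: longer window plus anticholinergic use**

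The rates are assumptions and are not in the documents. A class event occurs in 6% of patients per 42 days on an anticholinergic and in 2% off it, a true ratio of 3.0. A fraction q takes a non-study anticholinergic off study drug, equally after both treatments. There is no residual effect of tiotropium after the last dose. The mean off-drug window is 29 days, and 29/42 = 0.69.

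Added rate = 0.69 × [q × 6% + (1 − q) × 2%]

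| q | Added | Tiotropium | Placebo | Ratio | Difference |
|---|---|---|---|---|---|
| 0 | 1.4% | 7.4% | 3.4% | 2.2 | 4.0 points |
| 0.3 | 2.2% | 8.2% | 4.2% | 2.0 | 4.0 points |
| 0.6 | 3.0% | 9.0% | 5.0% | 1.8 | 4.0 points |

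The fall from 3.0 to 2.2 occurs with no non-study anticholinergic at all, simply because background events accumulate over more days. Anticholinergic use adds the step from 2.2 to 2.0 or 1.8.

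**3. Illustration B: anticholinergic use alone**

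These rates are also assumptions. True risks are 10% on tiotropium and 3% on placebo. A fraction p of patients takes a non-study anticholinergic off study drug, and a fraction r of those has a class event. All 124 randomized patients are taken to receive placebo once.

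- Patients added under placebo = 124 × p × r. For p = 10%, r = 5% this is 0.6. For p = 50%, r = 10% it is 6.2.
- Tabulated risk = 1 − (1 − true risk)(1 − p × r).
- At p × r = 0.005: 10.45% and 3.485%, ratio 3.00.
- At p × r = 0.05: 14.5% and 7.85%, ratio 1.85.
- The true ratio is 10/3 = 3.33. The difference is 7.0 × (1 − p × r) points, so it moves only from 7.0 to 6.65 at the upper end.

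**The case against.** The strongest reply is that the rule is an ordinary residual-effect convention and fits the protocol's own logic. Section 4.2.2 asks for four weeks off long-acting anticholinergics before Visit 3, the periods are four weeks apart, and serious events are reportable for 30 days after study medication ends. Charging events over that interval to the last study drug keeps late tiotropium events from being lost. This stands as a reason to keep the attribution. It does not explain why events on an active anticholinergic should go unmarked in the placebo column, since placebo has no residual anticholinergic effect.

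Other parts of the reply also stand:

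- Both columns are affected, so the difference is largely preserved if use is equal.
- Section 7.3.3 calls the safety analyses descriptive, plans no test and names no ratio.
- Exposure is limited. In the wash-out it is ipratropium, and only in baseline users. In follow-up, tiotropium is permitted but neither supplied nor scheduled.
- Section 8.4.1 has the investigator judge causality with concomitant medication as a confounder, and Section 7.3.3 tabulates that judgement. This helps, but the event still counts in the placebo frequency.

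A reader might infer that the rule conceals tiotropium's class effects, or that non-study anticholinergics drive most of the dilution. The documents support neither. In illustration A most of the dilution is background events, and no document gives the number of users. A reader might also suspect unequal use, because Section 6.3 (criterion 9) lets patients leave when the investigator judges maintenance tiotropium necessary. That this would be commoner on placebo is plausible, but it is not stated.

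**Conclusion.** The point holds in a limited form. Followed as written, Section 7.3.3 can place an event that began on ipratropium or marketed tiotropium in the placebo column, within windows that are 40% and 42% off study drug on the planned schedule. The direction is clear: a higher placebo incidence and a diluted ratio. The amount is not known. The illustrated ratios of 3.0 falling to between 2.2 and 1.8, and 3.33 falling to between 3.00 and 1.85, rest wholly on assumed event rates and assumed use, and the first also on no residual effect of tiotropium. The absolute difference changes little under equal use. This is an inexpensive improvement to a descriptive display. It is not an error that invalidates the safety analysis, and it implies no change to permitted medication.

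**What to change.** In Section 7.3.3, keep the current attribution and add a split within each treatment's adverse event table:

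- on-treatment events, with onset from first to last dose of the period plus a residual interval that the sponsor defines;
- later wash-out or follow-up events, shown by preceding treatment.

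Flag any event whose onset falls during use of a non-study anticholinergic. Do not end a patient's observation at the first such intake: patients with symptoms are more likely to start one, so that cut-off would be informative.

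No new data are needed. Event onset dates are source data (Section 8.2.4), and therapy start and stop dates are recorded throughout the trial (Section 4.2), with events and therapies collected again at Visit 7. The cost is revised wording, one more table set, and fewer events in the on-treatment display.
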